### Control arm: self-study group

Participants assigned to the control arm will work with their assigned Service Navigator for two sessions. During the first session, participants will receive the Health Coaching and Service Navigation workbooks, complete the baseline intake service navigation survey, and will be instructed that they will independently engage with the curriculum using the workbook or the study website (via a personalized log-in which tracks module completion). During the first session, the Service Navigator will assist the participant to establish their study website log-in credentials and how to access the Health Coaching modules on the study website. Participants who prefer to complete the printed curriculum will be instructed to submit photographs of the completed workbook pages to the study email to receive certificates of completion; these may be shared with their supervising officer or the court to demonstrate participation in activities that can benefit the participant reenter the community. During the second study visit, participants will receive a printed and digital (emailed) service navigation report which identifies recommended service providers and resources, including contact information so the participant can access these resources independently. Participants will have opportunities to ask clarifying questions at this visit and no further contact with the Service Navigator will occur.

### Baseline service navigation intake survey

Service Navigators will be trained to administer the baseline survey (~ 60 min) which is foundational to developing the individualized Service Navigation plan. Surveys will be accessed via password-protected computers which connect to the HIPAA-compliant Qualtrics survey software (Qualtrics, 2005). Participants will be interviewed in private spaces to protect confidentiality and receive a $20 gift card at the first visit.

### Dependent variables

Our primary outcome, recent use of health services is a dichotomous measure defined as any healthcare use in the past 6 months (vs. never received services or received services more than 6 months ago) (CDC/NCHS, 2021). Our secondary outcomes include health insurance status (defined as: uninsured vs. any insurance), type, continuity, and reasons for discontinuity or uninsured status, having a regular source of care (yes vs. no), care seeking (i.e., has delayed getting medical care in the past 6 months), and number of days in hospital (CDC/NCHS,^2021^).

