Addressing health literacy among JIA is important given the higher burden of illness among this sub-group as compared to the general population (Hawks et al., 2020). For example, significant proportions of JIA are impacted by chronic conditions that require regular monitoring and care such as chronic pain (47%), hypertension (34%), asthma (27%), Hepatitis C (24%), arthritis (22%), HIV (14%), and diabetes (13%) (Beckwith et al., 2010; Wang et al., 2012). JIA’s ability to navigate patient-centered care may be complicated by low educational attainment or underdeveloped basic skills (e.g., reading, numeric literacy); moreover, restrictions on self-care in carceral settings may impede development of these skills (Kindig et al., 2004; National Institutes of Health Network of the National Library of Medicine, 2020; Puglisi et al., 2017; Walsh-Felz et al., 2019; Wang et al., 2019). Extant research also finds that low personal health literacy is also associated with reduced use of preventive healthcare, increased use of emergency care, and higher mortality (Berkman et al., 2011; Kindig et al., 2004). Thus, addressing low personal health literacy is a national priority, and strategies tailored to justice impacted adults’ needs are required (U.S. Department of Health and Human Services, 2023).

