Two promising strategies that may support JIA and their health literacy include Health Coaching and Service Navigation. Health Coaching is a patient-centered strategy that seeks to build health literacy (Logan et al., 2015) and can be delivered by clinicians or health or peer educators (Ghorob et al., 2013). This approach has been used successfully to help patients manage chronic conditions and improve medication adherence. Health Coaching is associated with improved shared decision-making, information sharing, behavioral changes (Ghorob et al., 2013) and reductions in inpatient and total health care costs (Jonk et al., 2015). Service Navigation may be paired with Health Coaching with the goal of overcoming barriers to services that support well-being (Bernie et al., 2021; Carter et al., 2018; Fox et al., 2014). For example, an estimated 26% of JIA are uninsured (Hawks et al., 2020) and a lack of insurance or a regular source of care can contribute to delaying or forgoing care (Agency for Healthcare Research and Quality, 2018; Hadden et al., 2018). JIA are more likely to utilize emergency care or be hospitalized than the general population (Hawks et al., 2020). JIA also encounter persistent barriers to accessing related services to address the social determinants of health (e.g., employment, housing, nutrition support) and may be challenged when navigating complex systems of care in the community (KUSI Meade & Mellgren, 2011; News, 2020; Patel et al., 2014). Both Health Coaching and Service Navigation can help patients develop or improve executive functioning skills (e.g., goal setting, time management, resource procurement) that are transferrable across diverse settings (e.g., work, school) (Ojeda et al., 2021). Both approaches also provide social support and mentorship and can help individuals build resilience in the face of structural and social challenges (Teggart et al., 2023).

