### Pilot study

We first conducted a feasibility study between 2016–2020 in San Diego, California. We piloted a health literacy intervention that jointly implemented Health Coaching and Service Navigation among a sample of adults ages 18–26 under supervision of the local probation department (*n* = 148). The study sought to increase participants’ healthcare utilization (i.e., recent doctor visit, health insurance coverage, having a usual source of care). Participants provided written informed consent to receive 12 weeks of health coaching and up to 6 months of weekly service navigation support. The intervention was delivered in-person; additional service navigation support was provided by phone or text messages if requested (Ojeda et al., 2021). At 6-month follow-up, a subsample of participants (*n* = 66) that were retained until 6-months reported statistically significant improvements in two indicators of healthcare access. Specifically, participants reporting having a doctor visit in the past 6 months increased from 36% at baseline to 71% at 6-months (*p* < 0.001), health insurance coverage increased from 64% at baseline to 88% at 6-months (*p* < 0.01) and the proportion of participants reporting a usual place of care rose from 55 to 70% at 6-months (*p* = 0.09) (Ojeda et al., 2024).

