### Interventionist credentials & training

For this study, the interventionists will include Health Coaches and Service Navigators. *Health Coaches* will have graduate-level training as licensed therapists (e.g., Marriage & Family Therapist), prior experience serving JIA and deep knowledge about the region. *Service Navigators* will be community members with lived experience or history of serving JIA by providing community resources per participants’ needs (e.g., gender, race/ethnicity, faith, geographic region, income level). Navigators may have university-based education (e.g., Associate of Arts, Bachelor of Arts, Master of Public Health, etc.) in fields adjacent to social services or health professions, but this is not required. Service Navigators will have established relationships with local institutions that explicitly serve the study’s target population.

Health Coaches will undergo standardized training of the intervention, including studying written training manuals, the Health Coaching curriculum workbook, and training videos that describe the intervention philosophy, components and staff roles. Health Coaches will also meet with the principal investigator (PI), project manager, data analyst, and lead mental health faculty advisor to complete the training. The Health Coaches will have prior training in the use of patient-centered, team-based, trauma-informed, and strengths-based care, Mental Health First Aid, de-escalation techniques, SMART Goal Setting, and Case Management (Bath, 2008; Berghuis, 2018; Bjerke & Renger, 2017; Brun & Rapp, 2001; Conzemius & O'Neill, 2009; Epstein & Street, 2011; Gelkopf et al., 2016; Hadlaczky et al., 2014; King, 2017; Levenson & Willis, 2019; Rapp, 1998; Richmond et al., 2012; SAMHSA, 2014a, 2014b; Wallace et al., 2011; Woods et al., 2013). Service Navigators will be trained in the study’s resource directory and key partners and best practices in survey administration and how to administer the online baseline intake survey. Service Navigators and Health Coaches will be trained in documenting services provided, incentives, and adverse events using the study’s case management system. The Health Coach and Navigator will receive ongoing supervision and annual refresher training. Administrative staff (i.e., PI, project manager, data analyst) will meet weekly with the staff to debrief.

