### Power & sample size

A total of 300 individuals will be enrolled into the study. The power calculation was based on the primary outcome of recent healthcare utilization over the study period (yes/no) and analyzed with a mixed-effects logistic regression. Power was conservatively calculated for recent healthcare utilization at baseline, 6 and 12-months based on the assumption that 60% of the treatment group and 40% of the control group would report recent healthcare use (Ojeda et al., 2021). Accounting for an intraclass correlation coefficient of 0.4 and considering 30% attrition (of the 300 enrolled at baseline), we anticipate we will need 208 participants (104/group) to detect an odds ratio of 1.8 of recent healthcare utilization between the intervention and control group with at least 80% power and 0.05 two-tailed alpha.

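### As worded, the primary outcome counts emergency and inpatient care as success and does not rule out the trial's own coaching sessions

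*Protocol article*

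**What the plan says.** **Outcome.** Under Dependent variables, the primary outcome is "any healthcare use in the past 6 months (vs. never received services or received services more than 6 months ago". The contrast is one of timing only; nothing is said about the kind of care or where it is given.

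**Acute care.** The Background states that "low personal health literacy is also associated with reduced use of preventive healthcare, increased use of emergency care, and higher mortality", and that "JIA are more likely to utilize emergency care or be hospitalized than the general population".

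**Narrower measure elsewhere.** The Pilot study section reports that "participants reporting having a doctor visit in the past 6 months increased from 36% at baseline to 71% at 6-months". The section on qualitative interviews also names lack of a recent doctor visit as an example of an access barrier at baseline in this trial.

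**Service type.** Study aims & quantitative hypotheses lists types of services used among the exploratory outcomes.

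**Coaching.** Health Coaches "will have graduate-level training as licensed therapists". Table 3 and the treatment-arm section give the treatment arm alone 12 coaching sessions of about 45 minutes over 6 months. The Intervention section calls coaching psychoeducational. Treatment participants may have up to 12 Service Navigator sessions; control participants have two.

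**The concern.** Two separate problems follow from the wording.

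First, the trial's objective is better healthcare access, but the endpoint can rise through events that the article itself associates with low health literacy or poor access. If coaching moves a participant from the emergency department to a clinic, the outcome stays at yes and the gain is not seen. If emergency visits rise, that scores as improvement. The data that would separate these cases are exploratory only, so no one is committed to reading them beside the primary result.

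Second, the outcome is what participants report. A treatment-arm participant who has met a licensed therapist repeatedly in the past 6 months could in good faith answer yes on that ground alone. A control participant has no coach, so any such misreporting would inflate the difference in one direction, at the time point where the main hypothesis is tested.

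**Working it through.** **1. The plan's own figure.** Power & sample size assumes "60% of the treatment group and 40% of the control group would report recent healthcare use" and states a need for "208 participants (104/group) to detect an odds ratio of 1.8" with "at least 80% power and 0.05 two-tailed alpha", an intraclass correlation of 0.4 and measurements at baseline, 6 and 12 months.
- Control 40%, odds ratio 1.8: odds 0.40/0.60 × 1.8 = 1.2, so the treatment rate is 1.2/2.2 = 54.5%.
- The two-proportion formula gives 184 per group at one time point. The factor for three measures is (1 + 2 × 0.4)/3 = 0.6, and 184 × 0.6 = 110 per group. Power at 104 is 77.6%.
- Attrition: 208/0.70 = 297, consistent with 300 enrolled.

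So 104 is approached but not reproduced. Also, 60% against 40% is an odds ratio of (0.60/0.40)/(0.40/0.60) = 2.25, not 1.8. These are separate matters. Here 104 per group serves only as a scale for the illustrations.

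**2. What the wording covers.**

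| Event in the past 6 months | Counts as worded? | Basis |
|---|---|---|
| Clinic or doctor visit | Yes | Definition |
| Emergency visit or hospital stay only | Yes | Definition; no setting excluded |
| Coaching session (treatment arm only) | Not stated | Called psychoeducational; given by licensed therapists |

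The 6-month look-back covers months 0 to 6, the planned coaching period. The 12-month look-back covers months 6 to 12 and should contain no coaching.

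**3. Coaching reported as healthcare (illustration).** Assume no true effect, the same rate p0 in both arms, n = 104 per arm, one time point, and a share f of treatment-arm non-users who report coaching. Then p1 = p0 + (1 − p0)f. With p̄ the mean of p0 and p1, the chance of a significant result favouring treatment is

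Φ{[p1 − p0 − 1.96√(2p̄(1 − p̄)/n)] / √([p1(1 − p1) + p0(1 − p0)]/n)}.

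For p0 = 0.40 and f = 0.10: p1 = 0.40 + 0.60 × 0.10 = 0.46 and p̄ = 0.43. The two standard errors are 0.0687 and 0.0685, so (0.06 − 1.96 × 0.0687)/0.0685 = −1.09, and Φ(−1.09) = 13.8%. The nominal chance in this direction is 2.5%, half of the two-sided 5%. The opposite tail adds only 0.2 points.

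| f | Treatment vs control | Odds ratio | Chance of significance |
|---|---|---|---|
| 5% | 43% vs 40% | 1.13 | 6.4% |
| 10% | 46% vs 40% | 1.28 | 13.8% |
| 20% | 52% vs 40% | 1.62 | 41.1% |

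The plan's odds ratio of 1.8 would arise from coaching alone at f = (0.545 − 0.40)/0.60, about 24%. With a higher true rate there are fewer non-users to misclassify: at f = 10%, p0 = 60% gives 64% vs 60% and 8.6%; p0 = 70% gives 73% vs 70% and 6.9%.

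**4. Acute care counted in both arms (illustration).** Suppose outpatient use were 60% vs 40%, and 20% of the remaining non-users in each arm had acute care only. Any use is then 0.60 + 0.40 × 0.20 = 68% vs 0.40 + 0.60 × 0.20 = 52%, and the odds ratio is (0.68/0.32)/(0.52/0.48) = 1.96 instead of 2.25. Equal acute use in both arms thus pulls the contrast towards no difference.

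**The case against.** The strongest reply is that most of this rests on what a condensed article does not say. The survey item comes from a cited national survey source, and neither that source nor the questionnaire is shown; either may restrict what counts. The repeated use of doctor visit, including for this trial's baseline, suggests that the item may be narrower than the definition reads. Coaching is labelled psychoeducational. Nine of the 12 required modules are core topics such as values, goal setting and insurance, and at most two of the 12 touch mental health, sleep or substance use. The shares in the illustration are assumed, and the planned analysis is a mixed-effects logistic model over three time points, not a two-proportion test at one. Any use against outpatient use is a legitimate choice of endpoint, and insurance, regular source of care, delayed care and hospital days are also assessed.

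Much of this stands. It means that coaching being counted is an open risk, not a known event, and that the 14% shows sensitivity and is not an estimate. It does not remove the point. The definition as printed does count acute care. A general survey item would also not be expected to mention this trial's own coaches, whatever else it restricts.

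Three stronger readings are tempting and are not supported:
- **Care in custody counts as success.** The Missing data section says only that reincarcerated participants may continue after returning to the community; it says nothing about care received in custody.
- **The 60% and 40% are not rates of this endpoint.** Power & sample size states them as rates of recent healthcare use, and their cited source is not shown.
- **The primary result could not answer the access question either way.** The specific aim is framed as healthcare utilization, and access is also judged on other outcomes.

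**Conclusion.** The point holds as a matter of definition. As worded, emergency and inpatient use count as success on the primary outcome, against the article's own account of what such use signifies, and the narrower doctor visit appears elsewhere for the same construct. A positive result would therefore need the service-type data beside it before it could be read as better access.

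For coaching, the article shows a plausible one-sided risk at the 6-month primary assessment and none expected at 12 months. A reader might infer that the intervention contact will itself produce a positive trial; the documents do not show that. The size depends entirely on an undocumented share: about 14% false positives if 10% of treatment-arm non-users report coaching, assuming a 40% rate in both arms, 104 per arm and a single time point, and less at higher underlying rates. This is a low-cost improvement to the outcome's wording and reporting. It does not show that the endpoint is invalid.

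**What to change.** 1. Add an instruction to the healthcare-use item in the 6- and 12-month surveys: respondents should not count meetings with their RELINK Health Coach or Service Navigator. It should be in place before 6-month surveys are taken, because study contacts may be impossible to separate from other care afterwards.
2. Keep the primary endpoint. State in its definition that emergency and inpatient care count, and pre-specify a supportive analysis of the same outcome restricted to outpatient (non-emergency, non-inpatient) use. Build it from the service-type items already planned, use the same model, and report it beside the primary result.

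Cost: a small departure from the wording of the source survey item, which slightly weakens comparison with that survey, and one extra analysis. Sample size, primary endpoint and conduct of the intervention do not change.

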### Covariates

Covariates mirror the concepts identified in the conceptual model. Predisposing variables include demographics factors (age, race/ethnicity, gender, sexual orientation, marital status, duration of residence in San Diego County, veteran and foster care status) (CDC/NCHS, 2021). Enabling items are education, employment, income, food security, housing status, informational and emotional social support, and transportation access (CDC/NCHS, 2021; Hahn et al., 2010; Hahn et al., 2014; Salsman et al., 2019; University of Michigan, 2007; USDA, 2012; Veterans Affairs, 2016; Williams et al., 2008). Need variables include self-rated health, and provider assessed health status (Cella et al., 2019; Center for Behavioral Health Statistics & Quality, 2019; UCLA Center for Health Policy Research, 2019). Mental health status is assessed using the Patient Health Questionnaire (PHQ-9), Generalized Anxiety Disorder Scale (GAD-7), and a Traumatic Event Screener (Elhai et al., 2008; Kroenke et al., 2001; Spitzer et al., 2006). Health Behavior items include sleep, exercise, diet, and substance use (CDC/NCHS, 2021; Center for Behavioral Health Statistics & Quality, 2019; Santiago et al., 2017).

### Follow-up surveys & incentives to support retention

We will provide escalating incentive gift cards for survey-based data collection visits conducted at 6-months ($30) and 12-months ($50); these data will enable the researchers to assess participants’ use of health-supporting institutions over time. At baseline, we will collect participant locator forms for up to 5 persons who can help contact the participant, if needed and send visit reminders via text/email/phone call, per participant preference. We will provide $5 participant gift cards for monthly check-ins over months 7–12 in order to promote participant retention.

### Statistical analyses for survey data

A separate password-protected document with participants’ names and study ID number managed by the database administrator will enable linkage of all surveys. Statistical analyses will incorporate the intent-to-treat (ITT) principle. Participants who are randomized will be included in the ITT population. A mixed-effects logistic regression (Liu, 2015) will be used to analyze the effect of the coach-guided intervention on the primary outcome, recent healthcare utilization (yes/no) over the study period. This approach captures the between-individual and within-individual variability due to the repeated measures. Time invariant covariates include gender and age at baseline in addition to other predisposing, enabling, and health behavior variables determined to be unbalanced at baseline (univariate *p* < 0.10) and associated with the outcome (univariate *p* < 0.15). Time-varying covariates include follow-up time, treatment assignment (intervention vs. control), and time-by-treatment interaction terms. The maximum likelihood estimation approach used in the mixed-effects model enables us to incorporate all participant data even among those with only baseline measures. Analyses will be conducted using Stata v16 (StataCorp., 2019). Methods analogous to the analysis of the primary outcome will be applied to secondary outcome measures: 1) health insurance and 2) a regular source of care. Bonferroni’s correction will be applied for multiple testing of secondary outcomes, so statistical significance will be compared to a *p* < 0.025.

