### *Study arms & randomization*

After being screened for eligibility, participants will be randomized 1:1 to the treatment or control groups, which are described below and summarized in Table 3. A stratified permuted block randomization will be applied to assess the effect of a health literacy intervention (UCSD RELINK) on recent healthcare use among JIA, comparing a coach-guided treatment group versus a self-study control group. A random permutation method with block sizes 4, 6, and 8 will be used where within each block, half the participants will be randomly assigned to the treatment group and the remaining half will be assigned to the control group. We will use data for biological sex at birth to determine which strata an individual will be assigned to (i.e., male or female) before randomizing the participant to an intervention group. Given the small proportion of female JIA, this approach ensures the treatment and control groups will be balanced within biological sex. The randomization list will be generated using Stata v16 (StataCorp., 2019).

**Table 3 Tab3:** Comparison of the UCSD RELINK intervention delivery by study arm

	**TREATMENT GROUP** **Coach-Guided**	**CONTROL GROUP** **Self-Study**
**Program Orientation**	** + **	** + **

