### Missing data

Data will be routinely monitored by the investigators to ensure completeness; it will be visually inspected for errors, omissions, and data outside the limit ranges. A Consolidated Standards of Reporting Trials (CONSORT) diagram will be produced at the end of the study (Schulz et al., 2010). We expect that study loss to follow-up will be moderate (30%) due to our multi-pronged retention approach. If participants are reincarcerated, they will continue to be eligible to participate once they return to the community if they are within the 12-month study participation period. Per our retention plan, substantial efforts will be made to ensure complete follow-up. Rates of missing data and loss to follow-up will be reported. For the primary aim, the mixed-effects regression will yield consistent regression parameter estimates provided that the missing data are missing at random, a reasonable assumption when there are sufficient covariates considered in the analysis (Liu, 2015). Alternative missing data strategies, such as missing data imputation strategies or propensity weighting, will be considered based on the degree of missingness in the data but will not be applied without extensive sensitivity analysis. Under these various missing data strategies, the statistical analysis will be run and compared for consistency. When serious deviations are observed, the impact of the missing data will be evaluated to see if that is the source of the discrepancy.

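### Beyond age and gender, the primary model admits covariates by baseline-imbalance and outcome p-values, cannot admit Need variables, and names gender where randomisation used sex at birth

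*Protocol article*

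**What the plan says.** In the protocol article, *Statistical analyses for survey data* fixes two covariates: "Time invariant covariates include gender and age at baseline". It then adds others by rule, "in addition to other predisposing, enabling, and health behavior variables determined to be unbalanced at baseline". Two tests must both be passed. The variable must be "determined to be unbalanced at baseline (univariate *p* < 0.10") "and associated with the outcome (univariate *p* < 0.15"). Time, arm and time-by-arm terms complete the model. The section does not say which of them gives the primary odds ratio.

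Three other sections bear on this:

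- *Study arms & randomization* sets the stratum: "We will use data for biological sex at birth to determine which strata an individual will be assigned to".
- *Covariates* says the covariates follow the conceptual model, whose domains in *Conceptual model* include Need. It lists "Need variables include self-rated health, and provider assessed health status". Gender appears there as a predisposing variable: "Predisposing variables include demographics factors (age, race/ethnicity, gender, sexual orientation, marital status". Sex at birth does not appear in that list.
- *Missing data* calls missing at random "a reasonable assumption when there are sufficient covariates considered in the analysis", with 30% loss to follow-up expected.

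**The concern.** This is a stated rule, not a detail left to the analysis plan, and it selects on the wrong property. In a randomised trial a baseline difference between arms is chance, so a significance test of it says nothing about whether a covariate is worth adjusting for. What makes adjustment useful is prognostic strength. The rule discards a strong predictor whenever it happens to be balanced, which is most of the time. The covariate set, and with it the reported odds ratio, is then settled only after outcomes have been compared.

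Two internal mismatches sit beside this. Need variables cannot enter even when imbalanced and prognostic, because the rule names only the other three domains. And the variable in the model is not the one used to stratify.

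A smaller point concerns missing data. The argument for missing at random leans on having enough covariates, while the rule selects on imbalance and outcome association and not on relation to dropout.

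**Working it through.** **The plan's own sample size.** The formula for two proportions (pooled variance, two-sided 0.05, 80% power), for a 15-point difference (55% vs 40%, OR 1.83), gives 173 per arm. The repeated-measures factor for 3 visits and ICC 0.4 is (1 + 2 × 0.4)/3 = 0.6, and 173 × 0.6 = 103.8, so 104 per arm or 208. Allowing for 30% attrition, 208/0.70 = 297.1, or 298 in even numbers, consistent with 300. No covariate adjustment enters this figure, so changing the covariate rule does not change it. (The stated 60% vs 40% is an OR of 1.5/0.667 = 2.25, not 1.8. That is a separate matter; I used both values below.)

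**Number of candidates.** My count from *Covariates*, leaving out age and gender: 6 predisposing, 8 enabling (informational and emotional support counted separately) and 4 health-behaviour variables, so 18. A plausible range is 12–20.

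**First screen alone** (independent covariates assumed):
- Expected number with p < 0.10: 18 × 0.10 = 1.8.
- Chance of at least one: 1 − 0.9^18 = 85% (72% for 12 candidates, 88% for 20).

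**Both screens:**
- A non-prognostic covariate enters with probability 0.10 × 0.15 = 0.015. At least one of 18 such covariates enters with probability 1 − 0.985^18 = 24%.
- A prognostic covariate passes the first screen about 10% of the time however strong it is. Simulated entry was 7–10%, so it is left out in 90% or more of trials.
- With 3 to 4 prognostic covariates among the 18, at least one covariate entered in 36–49% of simulated trials. Check for 3 prognostic covariates at 9.4% entry: 1 − 0.906^3 × 0.985^15 = 41%, against 42% simulated.

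**Effect on the planned type of model.** Random-intercept logistic regression, three visits, 210 participants with complete data, ICC 0.4, conditional OR 2.25, 18 candidates of which four are prognostic (log-OR 0.5 per SD), outcome screen applied to the 6-month outcome, 400 runs:

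| Quantity | No covariates | Plan's rule | Prognostic set fixed in advance |
|---|---|---|---|
| 6-month arm difference: SD of log-OR | 0.400 | 0.397 | 0.380 |
| 6-month arm difference: power | 53% | 55% | 61% |
| Time-by-treatment interaction: SD of log-OR | 0.497 | 0.497 | 0.497 |
| Time-by-treatment interaction: power | 44% | 44% | 43% |

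For the arm difference, (0.397/0.380)^2 = 1.09, so the rule forgoes the equivalent of about 9% more participants. When the rule selected something, the arm-difference OR moved by a median factor of 1.13 (95th percentile 1.29–1.31). The interaction OR moved by a median factor below 1.01 (95th percentile at most 1.02). The mean log-OR for the arm difference was almost the same in all three analyses (0.822, 0.825, 0.827), so the movement is from trial to trial and not a systematic bias.

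**Single-time-point logistic model, as a cross-check** (4,000 runs per scenario, OR 2.25). Power under the rule against the fixed set: 77% vs 81% (three covariates at 0.3 per SD), 70% vs 77% (three at 0.5), 56% vs 69% (four at 0.7). Here the gain comes through a larger conditional OR, not a smaller standard error.

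**Type I error.** Single time point: 3.6–4.7% under the rule, 4.9–5.1% with no covariates. Random-intercept model: 5.2–5.8% across analyses of the 6-month difference and the interaction, under the rule and with no covariates. No inflation.

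**The case against.** The best defence is that the planned model carries baseline as one of its outcome visits. The arm main effect is then the baseline difference, and the intervention effect is naturally read from the time-by-treatment interaction. On that term the covariate rule hardly matters, as the table shows. A mixed-effects OR is also already conditional on the participant, so time-invariant covariates mostly reallocate between-person variance. This stands, and it limits the finding. It does not dispose of it: *Study aims & quantitative hypotheses* words the hypothesis as a comparison of arms at 6 months, *Power & sample size* speaks of an OR between the groups, and the analysis section leaves the term unnamed.

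Several stronger readings are tempting, and the documents do not support them:

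- *The model has no fixed covariates and omits the stratum.* Gender and age are always in, and gender is a close proxy for sex at birth. The defect is a mismatch to align.
- *The model changes in 85% of trials.* That is the chance that at least one variable passes the first screen; entry needs both.
- *The test is invalid.* Type I error was not inflated, and no section says who runs the screens or whether they are blinded.
- *Missing at random collapses.* Age, gender and the observed outcomes stay in the likelihood, and *Missing data* allows imputation or weighting not tied to this covariate list. The argument is weakened, not removed.
- *PHQ-9 and GAD-7 are omitted Need variables.* They have their own sentence after Need. Self-rated and provider-assessed health are the clear omissions.

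**Conclusion.** The point holds, as an improvement worth making and not as a threat to validity. Three things follow from the text alone: part of the primary model is chosen by chance imbalance, the Need domain cannot enter despite being measured and in the conceptual model, and the stratification variable and the adjustment variable differ.

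The size depends on the estimand. For an adjusted 6-month arm difference, the rule costs about 6 points of power in the repeated-measures simulation (4 to 13 in the simpler model) and makes the OR move by a median factor of 1.13 when selection occurs. For the interaction the cost is negligible.

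These sizes rest on my assumptions: 18 independent candidates, the prognostic strengths given above, no attrition beyond the reduced sample, and a fixed set made up of the truly prognostic covariates, which is a favourable case. With 400 runs, each power figure has a Monte Carlo standard error of about 2.5 points (√(0.55 × 0.45/400) = 0.025), although the analyses share the same simulated data. The exclusion of prognostic covariates in about 90% or more of trials does not depend on those strengths, because the first screen alone passes only 10%.

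**What to change.** In *Statistical analyses for survey data*:

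1. Delete both univariate p-value screens.
2. Name a short fixed set from data already collected: sex at birth (the stratum), age, self-rated health, and one or two variables chosen now as likely predictors of healthcare use and dropout, such as housing status or PHQ-9. If Need is left out on purpose, say so.
3. State which model term, or combination of terms, gives the primary 6-month OR.
4. Report any imbalance-adjusted model as a sensitivity analysis only.

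The cost is a few sentences, written before outcomes are compared by arm, and a few degrees of freedom. The sample size is unaffected.
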